## **6.4 Data Monitoring**

Monitoring of the data will be undertaken every 12 months and summary analyses will be provided to the independent members of the Trial Steering Committee. No formal interim analyses are planned. This Committee will meet at least every 12 months and will have the responsibility to recommend whether to stop the study early. As a general guideline, a difference between arms should exceed three standard deviations for some mortality endpoint before a decision to stop prematurely is taken, although other factors will also have to be taken into consideration. The Steering Committee will be responsible for the final decisions on such issues.

## **6.5 Unblinding the Randomisation**

The study is a double blind, placebo controlled, randomised trial i.e. neither the doctor nor the woman will know who is on active treatment. However, should a participant decide to request a codebreak and is on anastrozole, she will be able to continue the remainder of the trial treatment unblinded. Should a participant decide to request a codebreak and is on placebo, she will no longer receive trial medication and will move to the post-treatment phase of the trial.

**The treatment code should only be broken in the following circumstances:**

- 1) Where the woman develops breast cancer
- 2) When a clinician considers there to be valid medical or safety reasons to break the blind
- 3) When a participant requests unblinding

The clinician must have a legitimate reason to break the blind such as when the study drug is likely to have a significant effect on the clinical management of the subject e.g. in the case of a severe adverse event where it is necessary for the clinician to know which treatment the subject is receiving before the subject can be treated.

A written request, detailing the reason for the code break and signed by the PI, should then be faxed to the national coordinating office. The request will then be passed to the central coordinating office where once approved, the code will be broken by the IBIS-II programmer and faxed back to the PI.

Where required by designated national sites (due to time differences), access to the information for code breaks can be made available via a secure website.

The treatment code is located on a secure server at the IBIS-II CCO. There is no intention to break the code at the end of the trial.

## **6.6. End of Trial**

The end of trial is defined as Last Patient Last Visit (LPLV). This will occur when the last patient completes both 5 years of active trial treatment + 5 years' annual post-treatment follow-up (10 years in total). Follow-up beyond 10 years, applicable to those participants that have reached this stage, should be considered as an observational element to the study. This will ensure continued annual follow-up of all participants until LPLV (2022).

## **7. Consent and Ethics Committee Approval**

The study has been approved by the North West Multi-centre Research Ethics Committee (MREC). The study will also require local approval at participating centres.

This study involves evaluation of medicines for an unlicensed indication and is being carried out under EudraCT no. 2004-003991-12. Non-negligent indemnity for women joining the study will be provided worldwide by Queen Mary's University of London.

All women interested in participating in the study will receive a patient information sheet (PIS) that explains the purpose of the study and warns of the potential short term and long-term side effects of anastrozole. The clinician (Principal Investigator (PI) or other persons delegated to take consent) will clarify and discuss any points arising from the information literature. Participants will then be required to sign an informed consent form (CF) prior to undergoing any tests. Consent may be taken by the research nurse if the PI has approved this delegation. In such circumstances the PI should be available if necessary, so that the participant may then re-discuss the study with the PI, who will then counter-sign the CF. Further information and counselling will be made available throughout the study in response to a woman's request or following significant new information on the side effects of anastrozole. This will be provided by the clinician or the research nurse appointed for this study. All women will be free to stop treatment at any stage, and it will be made clear that leaving the study will not prejudice any future management which may be needed.

Women will be asked to consent

- i) to join the study,
- ii) to have their past and future medical records, mammograms, etc. examined, including those in a cancer registry or death certificate,
- iii) to the storage of personal information for the purposes of the study,
- iv) for a blood sample at entry and on follow-up for risk factor biomarkers and study of genes related to disease risk,
- v) to access to any pathology specimen for anonymous testing for factors related to disease or side effects,
- vi) to receive additional questionnaires from time to time to obtain further relevant information.

All research tests involving DNA or immunohistochemistry will be performed blindly on a case-control basis and results will not be linked to individuals. Thus, it will not be possible to inform women of the results of any tests because of the anonymous nature of all testing.

Participants have been informed of PID data collection and continued storage for the purposes of long term follow up. To clarify this, the process was reviewed and approved by the National Information Governance Board for Health and Social Care (ECC 6-03(FT8)2012), now known as section 251 support from the Confidential Advisory Group.

## 9. Appendix

### Appendix 1 – Breast Cancer Prevention Trials

| Trial
(entry dates)       | Population
(size)                                    | Agent
(vs Placebo)                     | Intended
Duration of
Treatment |
|------------------------------|---------------------------------------------------------|-------------------------------------------|--------------------------------------|
| Royal Marsden
(1986-1996) | Increased Risk
Family History
(2,471)             | Tamoxifen 20mg                            | 5-8y                                 |
| NSABP-P1
(1992-1998)      | 1.6% 5y risk
(13,388)                                | Tamoxifen 20mg                            | 5y                                   |
| Italian
(1992-1997)       | Normal Risk
Hysterectomy
(5408)                   | Tamoxifen 20mg                            | 5y                                   |
| IBIS-I
(1992-2000)        | >2-fold risk
(7,139)                                 | Tamoxifen 20mg                            | 5y                                   |
| MORE
(1994-1998)          | Normal Risk
Osteoporotic
Postmenopausal
(7705) | Raloxifene 60mg
Or
Raloxifene 120mg | 3y                                   |

## Appendix 1 continued

### Summary Results of Prevention Trials

[figure not shown]

Forest plot of estimates of breast cancer incidence reduction for the prevention trials. The summary estimate for all the tamoxifen trials is OR = 0.62 (95% CI (0.54-0.72))  $P < 0.001$ . Test of heterogeneity for all tamoxifen trials gives  $P = 0.09$ . However, the results of the MORE trial are clearly different (Cuzick et al 2003).

## **Appendix 2. Summary of Drug Handling Guidelines**

### **Astra Zeneca Responsibilities:**

The drug handling company IPS(A) will supply to the IBIS London Office. The two formulations used in the trial will be packaged as bulk primary packs, in boxes of 100, and labelled with batch numbers and expiry dates of the product. Each primary pack will contain 224 tablets in an HDPE (High Density Poly ethylene) bottle.

The Active and Placebo Anastrozole will be supplied in Small 75ml HDPE Bottles. Bottles will be capped with tamper evident child resistant lids.

Drug supplies for the study will be stored below 30°C, with the placebo formulation separated from the active formulation.

### **IBIS Central Coordinating Centre Responsibilities:**

These are fully described in the Investigational Product Ordering, Labelling, Supplying, Handling & Storage for IBIS-II Clinical Trial Standard Operating Procedure (SOP).

### Appendix 3a. SAE reporting flow chart – open sites

**Flow diagram 1** Reporting of a SAR or Serious Adverse Event (SAE) for a clinical event of interest by CCO to relevant authorities during follow up (i.e. questionnaire follow up)

[figure not shown]

Follow up information on a SAR/SAE in clinical event of interest must be reported by the investigator to the CCO in 24 hours and by CCO to AZ in the same time frame as the initial report. i.e. 24 hours since receipt from investigator. 24 hour deadline refers to a timeline within the normal working hour schedule.

AZ may request specific follow up information which will be sent to the Investigator via the CCO. SAEs that are not related (i.e. not a SAR) or not relating to clinical event of interest do not have to be reported during the questionnaire follow up period.

For further details, please refer to the 'SAE Reporting - Investigator Responsibilities' SOP and the 'Operational Guide' SOP

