#### **4.5.1.2 Post-treatment Follow-up Questionnaires (PTQ) - Years 6 – 10**

After 5 years of active treatment, women will continue to be followed up for clinical events of interest including SAEs, via the 'post-treatment follow-up' CRF for a further 5 years.

These will specifically ask the patients about the following events: -

- Breast cancer and DCIS (endpoint not requiring reporting)
- Stroke or TIA
- Other cancers (except basal cell carcinoma, squamous cell carcinoma of the skin and carcinoma in situ of the cervix)
- Cardiovascular events e.g. angina, heart attack, hypertension
- Thromboembolic events e.g. deep vein thrombosis, pulmonary embolism, phlebitis
- Osteoporosis/Broken/fractured bone
- Deaths

The decision to collect events of interest rather than asking about all AEs is based upon the following

- 5x half-life of IMPs will be reached within 35 days i.e. a short time period and therefore long term monitoring is not required.
- Except for certain conditions (endometrial cancer, osteoporosis/fracture, cardiovascular disease), further side-effect either stop with IMP washout or are of negligible significance.
- The safety profiles of Anastrozole has already been well-established across multiple trials and long follow up periods (as of 31 July 2016, the total cumulative exposure figure for ARIMIDEX in the marketed setting is calculated to be in excess of 8 million patient years)
- This is an ageing trial population with many AEs meeting the definition of SAEs but that are not of direct relevance to the trial objectives. To date, approximately 6% of reported SAEs in the post-treatment phase have been defined as causally related by the site investigator. Efforts should be re-focused on the collection of events known to be IMP related and the identification of any emerging safety signals. A more defined scope of AE collection is therefore warranted.

- All identified SARs/SUSARS will meet expedited reporting timeframes.

Sites have the option to conduct this by clinic, phone, postal questionnaire or if the patient is not able to be contacted, consultation of hospital records. This will collect data required to meet the primary, secondary and exploratory objectives of the trial.

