### **SAEs during the follow up period:**

SAEs which are an event of interest (see section 4.5.1.2), should continue to be collected and reported to the IBIS-II CCO after a patient has completed active treatment i.e. during the annual post-treatment follow-up period by the PI/delegated clinician under expedited timeframes. AEs/SAEs in clinical areas other than those pre-specified will not be actively sought or collected within CRFs during the follow up period and should not be sent to IBIS-II CCO. However, if an investigator becomes aware of a SAR during the follow up period i.e. meets the definition of an SAE and in the investigator's judgement has a causal relationship to a study IMP, this should be reported by the investigator to the IBIS-II team using expedited reporting timeframes, regardless of whether the SAE is a clinical event of interest.

What to report as an SAE in the long term follow up period under expedited conditions:

- ✓ Cerebrovascular event/Stroke/TIA
- ✓ New primary cancers (except basal cell carcinoma, squamous cell carcinoma of the skin and carcinoma in situ of the cervix)
- ✓ Cardiovascular events e.g. angina, myocardial infarction
- ✓ Thromboembolic events e.g. deep vein thrombosis, pulmonary embolism, phlebitis
- ✓ Osteoporosis/Broken/fractured bone
- ✓ Deaths (including underlying cause of death)
- ✓ Any other AE meeting the definition of serious (see above) and in the opinion of the investigator is causally related to the IMP i.e. **all SARs**

What not to report as an SAE in the long term follow up period:

- ✗ New breast cancer or DCIS (endpoint not SAE)
- ✗ AEs that do not meet the definition of serious
- ✗ Pre-planned hospitalisations/elective surgery where the underlying condition does not meet the definition of an SAE
- ✗ Non-protocol specified SAEs (see above) that are not in the opinion of the investigator, related to the IMP

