## **Reporting of serious adverse events**

Investigators and other site personnel must inform London IBIS Central Office of all SARs and any SAE in a specified event of interest within 24 hours, of becoming aware of the event.

The electronic SAE CRF will be sent to the IBIS Central Coordinating Centre and a hard copy of the SAE CRF should be printed, signed by the local principal investigator (or other clinician(s) delegated the task of causality assessment of SAEs) and faxed to the IBIS Central Coordinating Centre as soon as possible ([contact])

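### The Appendix 3a exemption, read as written, drops unrelated listed SAEs and unlisted SARs that section 4.5.4.2 requires open sites to report

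*Protocol*

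**What the plan says.** Section 4.5.4.2 sets the duty in follow-up in two parts. Listed events are reported with no condition on cause: "SAEs which are an event of interest (see section 4.5.1.2), should continue to be collected and reported to the IBIS-II CCO". SARs are reported "regardless of whether the SAE is a clinical event of interest". On this point, its list of what not to report exempts only "Non-protocol specified SAEs (see above) that are not in the opinion of the investigator, related to the IMP". The reporting paragraph of the same section repeats the duty: sites "must inform London IBIS Central Office of all SARs and any SAE in a specified event of interest within 24 hours".

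Appendix 3a covers open sites during questionnaire follow-up. Its caption gives the same scope as the body: "Reporting of a SAR or Serious Adverse Event (SAE) for a clinical event of interest by CCO to relevant authorities during follow up". So does its sentence on later information: "Follow up information on a SAR/SAE in clinical event of interest must be reported by the investigator to the CCO in 24 hours". Its exemption sentence then says "SAEs that are not related (i.e. not a SAR) or not relating to clinical event of interest do not have to be reported".

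Section 4.5.1.2 gives the only figure that bears on size: "approximately 6% of reported SAEs in the post-treatment phase have been defined as causally related by the site investigator".

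**The concern.** The body text exempts an SAE only when two conditions hold together: it is unrelated and it is off the list. The appendix sentence exempts it when either holds. A reader who follows the appendix literally would not report an unrelated stroke, myocardial infarction, fracture, new cancer or death, and would not report a SAR of an unlisted type.

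The second group matters most. Section 4.5.4.2 says that events outside the list are not actively sought on the follow-up CRFs, so an unlisted SAR reaches the coordinating centre through the investigator's own report. Section 4.5.4.4 has AstraZeneca decide which reported SARs are SUSARs, and a SAR that is not reported does not reach that step. Section 4.5.1.2 defends the narrower event collection partly on the ground that effort will go to drug-related events and new safety signals, and the appendix sentence works against that.

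The sentence is still in force. Sections 4.5.1.2 and 4.5.1.3 keep open international sites on questionnaire follow-up after amendment 60. Section 4.5.4.4 points to Appendices 3a and 3b as the summary of safety reporting.

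**Working it through.** The plan states no figure to reproduce. The check is a comparison of two rules.

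**Rules.** Let R mean that the SAE is judged related (a SAR), and L that it is a listed event of interest.

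- Section 4.5.4.2: report if R or L. Exempt if not R **and** not L.
- Appendix 3a exemption, read literally: exempt if not R **or** not L. The complement is: report only if R **and** L.

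| Case | Section 4.5.4.2 | Appendix 3a exemption, literal | Agree? |
|---|---|---|---|
| Related, listed | report | report | yes |
| Related, not listed (unlisted SAR) | report | exempt | **no** |
| Not related, listed | report | exempt | **no** |
| Not related, not listed | exempt | exempt | yes |

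The rules conflict in 2 of 4 cases. The appendix's caption and its follow-up sentence side with section 4.5.4.2, so the appendix also disagrees with itself.

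**Size.** Among all reported post-treatment SAEs, let p be the related share, q the listed share and r the share that is both. The share on which the rules disagree is

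D = (p − r) + (q − r) = p + q − 2r.

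The protocol gives p = 0.06 and neither q nor r. Two extremes are compatible with p = 0.06:

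- the listed SAEs are exactly the related ones: q = r = 0.06, so D = 0.06 + 0.06 − 0.12 = 0;
- no related SAE is listed and every unrelated one is: q = 0.94, r = 0, so D = 0.06 + 0.94 − 0 = 1.

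Neither extreme is plausible, but together they show that the 6% figure does not fix the size.

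**Under an added assumption.** If the related share among *listed* SAEs were s, the literal sentence would exempt 1 − s of them:

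| Assumed s | Listed SAEs exempted, 1 − s |
|---|---|
| 3% | 97% |
| 6% (overall figure carried over) | 94% |
| 20% | 80% |

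The exempted share stays above half unless more than half of listed SAEs are judged related. All unlisted SARs are exempt whatever s is.

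**After rewording.** If the exemption requires not R and not L, the appendix reports R or L, and all four cases agree with section 4.5.4.2.

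**The case against.** The strongest reply is that this is a slip for 'neither ... nor' and that the rest of the document makes the intention plain. Section 4.5.4.2 has explicit lists of what to report and what not to report, its reporting paragraph uses mandatory language, and the appendix's caption and follow-up sentence agree with it. A site would have to follow one sentence against all of these. This stands as evidence of intention and as a reason not to claim that harm occurred. It does not remove the conflict: the exemption is an explicit permission not to report, and the protocol does not say which text prevails.

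A second reply is that outcome data are safe. For listed events this is right. The post-treatment CRF in section 4.5.1.2 asks about them directly and without regard to cause, and registry data add to this in the UK. It does not cover unlisted SARs, which that CRF does not ask about. At open UK sites the registry check in section 4.5.4.3 may bring an event to light, but confirming and reporting it as a SAR still falls to the site.

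A third reply is that the scope is narrow, and this is also right. On-treatment reporting and closed UK sites, which use registry line listings, are not touched. The flow diagram is not shown in the text reviewed, so it may already be correct.

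A reader might also infer that code breaks lead to unblinded causality opinions and so to biased SAE counts by arm. Code breaks on request are allowed (sections 4.5.3 and 6.5), but the document gives no figure for such an effect, and events recorded on the CRF would not be exposed to it.

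**Conclusion.** The contradiction is real. Read as written, one sentence in Appendix 3a exempts unrelated listed SAEs and unlisted SARs that section 4.5.4.2 and the appendix's own caption require to be reported. It applies to open sites in questionnaire follow-up only. The consequence is conditional on a site applying the sentence literally. Expedited reporting and SAE-level detail would then lapse for unrelated listed events, and unlisted SARs would lose the only reporting route described for them at open sites.

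Three stronger readings are tempting and not supported:

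- *That these events go unreported.* Nothing in the document shows that a report was withheld.
- *That secondary-outcome data are lost.* Listed events are still recorded on the post-treatment CRF.
- *That 94% of SAEs drop out because of the sentence.* The 6% covers all reported post-treatment SAEs, and its complement includes unlisted unrelated SAEs that section 4.5.4.2 exempts anyway. For listed SAEs, 94% is only what follows if the overall share is assumed to carry over, with 80% to 97% for shares of 20% to 3%.

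This is a drafting error in an operative safety rule. It should be corrected because the correction is cheap and unlisted SARs have no other reporting route to fall back on.

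**What to change.** Reconcile the Appendix 3a exemption with section 4.5.4.2. One wording that does so is: *An SAE needs no report during questionnaire follow-up only if it is neither a SAR nor a clinical event of interest.*

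Check that the flow diagram and the SOP on investigators' SAE reporting follow the same rule. Neither could be seen here, and both may already be right. Then notify open sites of the corrected sentence.

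The cost is one sentence in an appendix, a consistency check of two documents and a short notice. No new data item or duty arises, since section 4.5.4.2 already requires these reports.

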### Appendix 3b. SAE reporting flow chart – registry data

Reporting of clinical event of interest identified from digital registries (only once on-site data has stopped) by CCO to relevant authorities

[figure not shown]

For further details, please refer to the 'Operational Guide' SOP
